### Methods in analysis to handle protocol non-adherence and any statistical methods to handle missing data {20c}

Missing data will be reported in the publication and if it is not valid to ignore missing data we will consider computing best–worst and worst-best case scenarios.

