**Methods:**

Adult patients needing a tCDC will be included from several hospitals and randomised to either subclavian or internal jugular vein catheterisation with a silicone tCDC. Inclusion continues until 50 patients in each group have undergone a follow-up CT venography. The primary outcome is the incidence of post-catheterisation central vein stenosis detected by a CT venography performed 1.5 to 3 months after removal of the tCDC. Secondary outcomes include between-group comparisons of (I) the patients’ experience of discomfort and pain, (II) any dysfunction of the tCDC during use, (III) catheterisation success rate and (IV) the number of mechanical complications. Furthermore, the ability to detect central vein stenosis by a focused ultrasound examination will be evaluated using the CT venography as golden standard.

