### Sample size {14}

Sample size calculation for the primary outcome was performed using an online calculator (https://www.sealedenvelope.com/power/binary-noninferior/) based on results of a previous study [3] that demonstrated a CVS incidence of 10% after tCDC insertion in the internal jugular vein. The rate of stenosis events in historical data has ranged from 10% for the jugular vein to 42% for the subclavian vein. Given the perceived and shown advantages with subclavian lines (less infections/thrombosis, more comfortable for the patient during insertion and use), we chose a 15% noninferiority margin as this is less than half the absolute difference, is judged to be clinically acceptable and results in a reasonable sample size. Calculations revealed that 50 patients per group are needed to be 80% sure that the upper limit of a one-sided 95% confidence interval (or equivalently a 90% two-sided confidence interval) will exclude a difference in favour of the standard group. In order to have 100 patients perform the CT venography for the per-protocol analysis, at least 200 patients will probably have to be included in the trial. Important differences found between the treatment groups (in terms of how many that did not complete the protocol) will be reported.

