## Statistical methods

### Statistical methods for primary and secondary outcomes {20a}

The study aims to explore if the incidence of post-catheterisation CVS when using the right-sided subclavian route is non-inferior to the internal jugular route. All patients randomised in this trial will be analysed on a per-protocol basis. The primary outcome will thus be analysed only in patients subjected to the follow-up CT venography. Patients will be enrolled using previous exit rates to determine when the calculated sample size for both groups can be reached.

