### Baseline variables

Continuous variables following a symmetric distribution will be presented with mean (SD), while skewed variables will be presented with median (IQR). Ordinal variables will be presented with median (IQR) and categorical variables will be presented as *n* (%).

The primary outcome will be analysed as a binary variable (stenosis *vs* no stenosis) at follow-up and described using a 95% one-sided confidence interval for the absolute difference between the proportions, calculated as event rate intervention group − event rate control group. If the upper limit of the confidence interval is below the non-inferiority margin, the conclusion will be that the event rate in the intervention group is non-inferior to the event rate in the control group.

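### The only method named for missing primary outcomes, best–worst and worst–best scenarios, cannot inform a 15-point margin once more than about 5% per arm is imputed

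*Protocol article*

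**What the plan says.** The primary analysis is a complete-case, per-protocol comparison: "The primary outcome will thus be analysed only in patients subjected to the follow-up CT venography" (Statistical methods {20a}). The decision rule, under Baseline variables, uses a confidence limit and declares subclavian non-inferior when that limit clears the margin: "If the upper limit of the confidence interval is below the non-inferiority margin, the conclusion will be that the event rate". The margin is 15 percentage points (Sample size {14}).

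Heavy loss is expected: "In order to have 100 patients perform the CT venography for the per-protocol analysis, at least 200 patients will probably have to be included" (Sample size {14}). The section on non-adherence and missing data {20c} says that missing data will be reported and then gives one conditional method: "if it is not valid to ignore missing data we will consider computing best–worst and worst-best case scenarios".

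Three other provisions touch on the matter. Reasons for exit and exclusion are collected and reported ({11b}). Important between-group differences in protocol completion are reported ({14}). Baseline imbalance may lead to a stratified comparison ({20b}). None of these assigns or models an outcome for a patient without a CT.

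**The concern.** In these scenarios every patient with a missing outcome in one arm is counted as stenosed and every such patient in the other arm as free of stenosis, and then the reverse. The distance between the two results depends on the share imputed, not on what was observed. If that share is large against the margin, one scenario will fail and the other will pass for any plausible data, and neither helps a reader judge whether the complete-case result is robust.

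The trigger adds to the problem. Whether missing outcomes can be ignored depends on the unseen outcomes, so the observed data cannot settle it, and even then the analysis is only to be considered. A non-inferiority claim based on about half of those included could therefore be published with no working check on the missing outcomes, or with one whose answer was predictable.

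**Working it through.** **Inputs.** Margin 15 points, one-sided 95% limit, 80% power, 50 per group, jugular rate 10%, 100 scanned out of at least 200 included (all from {14}); equal target per arm (abstract, Methods). An equal 10% rate in the subclavian arm is an assumption. The protocol does not state it, but it reproduces the sample size.

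**The plan's own figure.** n per arm = (1.645 + 0.842)² × (0.10×0.90 + 0.10×0.90) / 0.15² = 49.5, so 50. This matches the protocol, and power at 50 is 80.4%. The step 100 / (1 − 0.5) = 200 gives the anticipated loss of about 50%.

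**Complete-case result.** 5/50 vs 5/50: difference 0, upper limit 1.645 × √(2 × 0.09/50) = 9.9 points. Non-inferior.

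**Formula.** With an equal imputed share m per arm and observed difference d (subclavian − jugular), the worst case for subclavian is (1−m)d + m and the best case is (1−m)d − m. The limits below are Wald limits.

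**Range of the imputed share**, 50 scanned and 5 stenoses in each arm:

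| Imputed per arm | Share | Worst case (upper limit) | Best case (upper limit) |
|---|---|---|---|
| 2 | 3.8% | +3.8 (14.1) | −3.8 (6.4) |
| 3 | 5.7% | +5.7 (16.1) | −5.7 (4.8) |
| 5 | 9.1% | +9.1 (19.8) | −9.1 (1.6) |
| 10 | 16.7% | +16.7 (27.6) | −16.7 (−5.8) |
| 20 | 28.6% | +28.6 (39.3) | −28.6 (−17.9) |
| 50 | 50% | +50.0 (58.9) | −50.0 (−41.1) |

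For example, 3 per arm gives 8/53 − 5/53 = 5.7 points, plus 1.645 × √[(0.151×0.849 + 0.094×0.906)/53] = 10.4, which is 16.1. On a continuous scale the crossing is at about 4.7%.

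**A result that favours subclavian.** 3/50 vs 7/50 with 10 imputed per arm: 13/60 − 7/60 = +10.0, plus 1.645 × √[(0.217×0.783 + 0.117×0.883)/60] = 11.1, upper limit 21.1. The worst case still fails.

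**The full 50%.** The scenarios are d/2 ± 50. With d = −10 they are +45 and −55. With the historical contrast of 42% vs 10% (d = +32) they are +66 and −34, so the best case passes (upper limit −23) on data showing a 32-point excess. The worst-case point estimate falls to 15 only when d = −70 (0/50 vs 35/50), and its upper limit is then still 26. Uneven loss of 60%/40% with 10% observed in both arms gives +58 and −42.

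**What a tipping point would show.** Take 50 scanned and 10 unscanned per arm, with 10% in all jugular patients (6/60) and in scanned subclavian patients. If 4 of the 10 unscanned subclavian patients had stenosis: 9/60 − 6/60 = 5.0, plus 1.645 × √[(0.15×0.85 + 0.10×0.90)/60] = 9.9, upper limit 14.9. If 5 of 10 did: 10/60 − 6/60 = 6.7, upper limit 16.8. The conclusion turns when the unscanned rate lies between 40% and 50%, against 10% in scanned patients. This sketch treats imputed values as observed; allowing for imputation uncertainty would widen the interval and lower the tipping point.

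**The case against.** The strongest objection is that the 50% is not all missing data. It is an expectation, worded with "at least" and "probably", and it covers every way of leaving the per-protocol set. That includes failed placement in the randomised vein, incorrect tip position, dwell below 7 days, a second right-sided catheter and death ({11b}). The hypothesis concerns use for at least 7 days, so many of these patients lie outside the question, and no split is given. This stands. A reader might infer that the scenarios will always give about ±50 points, fixed by design. The protocol does not support that: the result moves with the observed difference, the balance of loss and the share actually imputed.

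A reader might also place the breaking point at a loss of about 15% per arm. That is where the worst-case point estimate reaches the margin when observed rates are equal. The trial decides on the upper limit, which crosses earlier, at about 5%.

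Nor is the complete-case result wholly unexamined, since exits, completion differences and baseline imbalance are reported or tested. These steps describe the loss, but they do not show what it could do to the conclusion.

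Finally, imputation models and delta grids usually belong in a statistical analysis plan, which may exist, and extreme bounds are a legitimate device. Both are fair. The point is therefore not that detail is absent. The protocol names a method, and that method does not suit its own margin and expected loss. Multiple imputation as a required replacement would also be debatable, with about 10 events expected in total (10% of 100).

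**Conclusion.** The concern holds in this form: the one method the protocol names for missing primary outcomes cannot discriminate against a 15-point margin at the loss it expects. With equal observed rates of 10% and 50 scanned per arm, the worst case breaches the margin once about 5% per arm is imputed. The upper limit is about 16 points with 3 imputed per arm, about 28 with 10, and about 59 if the whole anticipated 50% were imputed. The last figure is an upper assumption.

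The conclusion does not need the 50%. It needs only an imputed share above roughly 5% per arm, and death and low eGFR without dialysis are among the protocol's own listed reasons for having no CT. The threshold assumes equal observed rates, equal loss and Wald limits, and would shift somewhat under other values. The primary analysis itself is not invalidated; its only named safeguard for missing outcomes is uninformative and optional.

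**What to change.** Amend {20c} as follows.

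- Commit, without a condition, to a delta-adjusted tipping-point analysis. Define its population as patients who meet the per-protocol question but have no CT: randomised vein catheterised with correct tip position, tCDC in place at least 7 days, no second right-sided catheter, alive at the CT window.
- Report how much higher the stenosis rate in unscanned subclavian patients must be than in scanned ones before the one-sided 95% upper limit reaches 15 points. Fix the range of deltas, and the assumption for unscanned jugular patients, before the data are seen.
- Report deaths and each other reason for exit or exclusion by arm, so that readers can see how much of the loss is truly missing outcome.
- Keep the best–worst and worst–best scenarios only as outer bounds.
- Treat multiple imputation within arm as optional, because few events are expected.

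The cost is a little more analysis work and the need to pre-specify the delta range. Recruitment, follow-up and the primary analysis are unchanged.

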### Plans to give access to the full protocol, participant level-data and statistical code {31c}

All data and statistical codes will be available upon reasonable request.

## Oversight and monitoring

### Composition of the coordinating centre and trial steering committee {5d}

The trial steering committee, including representatives from all participating departments, is anticipated to meet quarterly during the trial. The committee does not contain independent members who are not participating. Dedicated research nurses will assist the trial on a day-to-day basis.

### Composition of the data monitoring committee, its role and reporting structure {21a}

Data monitoring will be performed by an independent data monitoring committee (DMC) that consists of members of the Clinical Research Unit, Skåne University Hospital, in Lund.

### Frequency and plans for auditing trial conduct {23}

Each site will have monitoring done at three occasions: before study start, early during the trial (after approximately 10 patients have been included at the site) and when the last patient has performed the CT venography. Dedicated research nurses, without co-authorship in the current study, will monitor the data inserted in the eCRF on a monthly basis.

The trial steering group will meet at least every second month to review trial conduct. The trial steering group and the DMC meet to review conduct throughout the trial period.

### Adverse event reporting and harms {22}

Any event that has a reasonable, causal relationship to the study intervention will be deemed an adverse event (AE). All patients are evaluated with regard to potential AEs or serious adverse events (SAE) by one of the investigators. Potential AEs and SAEs are recorded in the eCRF and should be hastily reported to the chief investigators for decisions on any change in the protocol. Furthermore, the DMC will be notified whenever there is a serious adverse event.

### Plans for communicating important protocol amendments to relevant parties (e.g. trial participants, ethical committees) {25}

Important changes in this protocol will be reported to the National Ethical Review Board, Sweden, and an amendment approval will be sought. Further, important changes will be registered in ClinicalTrials.gov and communicated to the site investigators, research nurses and monitors by established networks.

### Dissemination plans {31a}

The main manuscript describing the results of the current trial will be submitted to a peer-reviewed journal regardless of the results of the trial. Authorship will be determined in accordance with the International Committee of Medical Journal Editors and detailed criteria needed for co-authorship will be decided in advance.

## Discussion

The CITES trial is designed to provide robust data on whether the incidence of CVS after insertion of a silicone tCDC in the right subclavian vein is non-inferior compared to when using the internal jugular vein. This is clinically important as the subclavian route offers several advantages for the patient (e.g. less infectious and thrombotic complications) and because other routes are sometimes unavailable for catheterisation.

The current study is not an evaluation of a clinical routine but rather aims to explore the proof of concept that the subclavian route is non-inferior to the internal jugular route with regard to the incidence of post-catheterisation CVS. This design is based on the knowledge that older studies [3, 14] were performed with stiff polyurethane catheters and had methodological issues such as lack of randomisation, varying definitions of CVS and selection bias (e.g. only patients with a clinical indication for CVS investigation were included).

To allow for thrombosis and any temporary narrowing of central veins to resolve, a time interval for the CT venography of 1.5–3 months after removal of the tCDC was chosen.

Data from the era of landmark-based catheterisations have indicated less misplacements when using the left-sided subclavian vein [15]. However, right-sided catheterisation was chosen for this study as it allows for having the supraclavicular fossa view within the sterile field, which makes real-time ultrasound-guided navigation of the guidewire tip possible [16]. Furthermore, the right internal jugular vein is the vein of choice for dialysis catheters [17], right-sided catheters are generally 5 cm shorter than the left-sided ones which will allow for less resistance to blood flow [18] and less catheter area is exposed to the veins.

The administration of intravenous contrast within the study is done in accordance with the European Society of Urogenital Radiology (ESUR) guidelines [19]. Thus, patients with severe renal failure (GFR < 15 mL/min/1.73 m^2^) without ongoing dialysis at follow-up will be excluded from the study as intravenous contrast can affect the renal function in patients with renal impairment [14]. The amount of contrast and the radiation dose administered to the patient have been minimised in the current protocol.

Real-time ultrasound guidance is used in > 93% of central venous catheterisations at the hospitals within Region Skåne (unpublished data). Thus, it would seem prudent to also make use of the ultrasound equipment to verify that the central veins are patent prior to the procedure to save time and avoid added patient discomfort. In order to gain acceptance and allow for easy implementation, the protocol is kept simple (Additional file 5).

## Trial status

Recruitment started on November 15, 2021, and is anticipated to end by December 2025.

## Data Availability

This document constitutes the full protocol. Following the completion of the trial datasets used in this study, it will be available from the corresponding author on reasonable request.

## Abbreviations

AV fistula: Arteriovenous fistula
BMI: Body mass index
CT: Computed tomography
CVS: Central vein stenosis
PICC-line: Peripherally inserted central catheter line
tCDC: Temporary central dialysis catheter
